**Methods:**

A two-arm randomised controlled trial will be conducted. We aim to recruit 150 COPD patients for whom NIV is indicated. The experimental group will receive a brief course of psychological support that will include counselling, relaxation and mindfulness-based exercises. In some cases, it will also include neuropsychological rehabilitation exercises. Support will be delivered via four to eight meetings at the HD Respiratory Rehabilitation Unit, at home or via telemedicine. Controls will receive standard care and watch educational videos related to the management of their disease.

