Patterns of acceptance of non-invasive ventilation (NIV) are examples of the interaction of psychological and physical factors. Despite the fact that NIV can produce significant clinical improvement in their condition, patients often reject it or fail to use it appropriately. NIV rejection or its inappropriate use results in worse clinical outcomes and increased health care costs. Appropriate use of NIV is crucial, given that adherence to medication decreases over time and is inversely related to the number of drugs prescribed [23, 24]. Acceptance and adherence to NIV treatment can reduce hospital admissions and physician visits [25]. Using NIV requires the patient to make some behavioural and lifestyle changes, such as changes in daily routine to allocate time for ventilation, and this may reduce adherence to the treatment [24]. Treatment adherence may also be adversely affected by the use of different drugs and devices, or because patients receive inadequate education about the illness and associated morbidities from their physician [26, 27].

Clinical experience suggests that patients with cognitive deficits [12, 28, 29] or psychological problems, such as anxiety and depression, are less likely to accept and comply with NIV regimes; however, there has been little research on this. The few available studies focussed on early NIV failure (defined as the need for endotracheal intubation or death within 24–48 h of starting NIV) [30, 31], quantifying adherence [32] and largely neglected predictors of nonadherence [33]. No study has identified the individual psychological factors that increase the risk of rejection or improper use of NIV. Previous studies suggest that COPD patients who clearly demonstrated a lower survival benefit from the NIV usage exhibit worse average daily NIV adherence, because of the imbalance between the constraints that NIV imposes and the improvement that patients’ perceive in their condition [34]. Ventilator settings are not easy to adjust and they influence sleep quality, which has spill-over effects on daytime life [34, 35]. The effects of psychological support in promoting the machine’s acceptance have also not been adequately investigated.

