### Objectives

The primary objective of the study is to evaluate the effects of psychological support on the acceptance of, and adherence to, NIV. Secondary aims include assessment of the change in QoL between baseline and after 3, 6 and 12 months following recruitment, identification of psychological and clinical factors that predict rejection or misuse of NIV, and factors that predict the success of the psychological intervention.

The primary outcome will be a latent variable related to indices of use of NIV equipment and adherence to treatment regime: the effects on change from baseline in acceptance to NIV in COPD patients at 3, 6 and 12 months as measured by weekly means and standard deviations of hours of use of NIV as recorded by the ventilator and changes in adherence defined as the difference between prescribed and effective NIV hours. Change in QoL will also be measured relative to baseline at 3, 6 and 12 months using the EuroQoL (EQ-5D) questionnaire, respiratory, functional and biomedical parameters. Survival rates after starting the adaptation to NIV and psychological variables will be considered as secondary outcomes.

As well as evaluating clinical and psychological variables we will also evaluate econometric outcomes. The study will explore the potential impact of the psychological intervention on the cost to the Italian welfare system of providing health care for patients with COPD. These assessments will be based on standard econometric indices (e.g. quality-adjusted life years (QALYs); DALYs).

Finally, semistructured interviews will be conducted to gain insight into patients’ perceptions of NIV.

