### Sample size

Based on statistical analysis, preventive inherent power and sample size [40] we anticipate that the study will require 150 subjects. We will recruit between 128 subjects (statistical power of 0.80; *α* = 0.05; 1 − *β* = 0.80; *t* (126) =1.97) and 172 subjects (statistical power equal to 0.90; *α* = 0.05; 1 − *β* = 0.90; *t* (170) = 1.97). The inherent power also emphasises that such analyses have been carried out using data for a scientific study that have a comparable primary outcome [33].

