### Proposed analyses

Descriptive analyses will be performed for all study variables. We will assess the effect of the interaction between treatment (experimental versus control) and time (three repeated measures) on primary outcome variables (acceptance of treatment; adherence to treatment). Missing data will be imputed with multiple imputation techniques [58, 59].

Before-after differences will be analysed with appropriate within-group tests (paired samples *t* test; Wilcoxon test). Multiple regression will be used to assess the influence of baseline variables on outcome indicators and identify predictor variables.

The analysis will be performed using the intention-to-treat procedure. The significance level will be 5% (*p* ≤ 0.05). Data analysis will be performed using SPSS software.

Data collection and analysis will begin in month 1 and will last for 24 months, i.e. until 1 month after the last follow-up data have been collected.

We will report reasons for withdrawal for each randomisation group and compare the reasons qualitatively. The effect that any missing data might have on results will be assessed via sensitivity analysis of augmented data sets. Dropouts (essentially, participants who withdraw consent for continued follow-up) will be included in the analysis by modern imputation methods for missing data.

For more details about the trial, refer to the SPIRIT Checklist (Additional file 1).

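### No test of the randomised contrast is stated for quality of life, psychological or clinical scales; the only further test of change is within-group

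*Protocol article*

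**What the plan says.** The design is between-arm: "A two-arm randomised controlled trial will be conducted" (abstract, Methods).

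The Proposed analyses section of the protocol article then gives three inferential elements:

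- The interaction of treatment with time, stated for the primary outcome variables, with acceptance and adherence named in brackets.
- "Before-after differences will be analysed with appropriate within-group tests", with the paired t test and the Wilcoxon test given as the methods. No outcome is attached to this sentence.
- Multiple regression of outcome indicators on baseline variables, to find predictors. Treatment arm is not named as a term.

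The Objectives section frames quality of life as change over time: "Secondary aims include assessment of the change in QoL between baseline and after 3, 6 and 12 months following recruitment". It also lists survival and the psychological variables as secondary outcomes. The Assessment section adds fatigue, spirometry and blood gases, and places EQ-5D among the psychological measures.

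The Discussion hopes, if the hypothesis is confirmed, to credit the intervention with benefits to physical and psychological wellbeing. It also presents the comparison with an active control group as a strength of the design.

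**The concern.** A paired test inside one arm asks whether that arm changed. It does not ask whether support changed patients more than the control condition did, which is the question randomisation was set up to answer.

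Change common to both arms is plausible here. The patients are those for whom NIV is indicated, the Background says that "NIV can produce significant clinical improvement in their condition", and controls receive standard care plus educational videos. A before-after test in the support arm absorbs all of that. Comparing two within-arm p values does not rescue it, because a significant result in one arm and a non-significant one in the other is not a test of the difference.

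At stake are the statements on quality of life and wellbeing. If the analysis follows the article as written, a claim that support improved them could rest on tests that make no use of the control arm.

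**Working it through.** **1. What the trial was sized for.** The article gives "128 subjects (statistical power of 0.80" and "172 subjects (statistical power equal to 0.90", and says "we anticipate that the study will require 150 subjects". It states no effect size. A two-sample t test with two-sided 5% alpha, 1:1 allocation and an assumed standardised difference of 0.5 gives totals of 128 and 172 (exact noncentral t; the normal approximation gives 126 and 170). Assumed differences of 0.4, 0.45, 0.55 and 0.6 do not give both figures. So the stated sizes are those of a comparison between arms. At 150 patients, power for a difference of 0.5 is 86%.

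**2. Inputs for the illustration.**
- Alpha: "The significance level will be 5"%, taken as two-sided because the stated critical t is about 1.97.
- Patients per arm: 150 / 2 = 75. The allocation ratio is not stated, so 1:1 is an assumption.
- True change m, in SDs of change, identical in both arms, so there is no treatment effect. The documents give no value; the range used is 0 to 0.5.
- Decision rule: support arm significant, control arm not. This is also an assumption; the article states no rule.

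**3. Formula.** Each arm's paired t test has 74 df, critical value 1.993 and noncentrality m × √75 = 8.660 m. Let p be the chance that one arm is significant. The arms are independent, so the chance that only the support arm is significant is p(1 − p), and the chance that exactly one arm is significant is 2p(1 − p).

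**4. Results, 75 per arm, no treatment effect.**

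| Common change m (SD) | Noncentrality | p, one arm significant | p(1 − p), support arm only | 2p(1 − p), exactly one arm |
|---|---|---|---|---|
| 0 | 0 | 0.050 | 4.8% | 9.5% |
| 0.1 | 0.866 | 0.137 | 11.8% | 23.6% |
| 0.2 | 1.732 | 0.401 | 24.0% | 48.1% |
| 0.23 | 1.992 | 0.502 | 25.0% | 50.0% |
| 0.3 | 2.598 | 0.727 | 19.8% | 39.7% |
| 0.33 | 2.858 | 0.805 | 15.7% | 31.4% |
| 0.4 | 3.464 | 0.928 | 6.7% | 13.4% |
| 0.5 | 4.330 | 0.990 | 1.0% | 2.0% |

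With 64 or 86 per arm (totals 128 and 172) the highest value of p(1 − p) on the same grid is still about 25%.

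**5. The between-arm alternative.** In 20,000 simulated trials at each of m = 0, 0.2, 0.23, 0.3 and 0.5, a two-sample t test on the changes rejected in 4.8%, 5.0%, 4.9%, 4.9% and 5.2%.

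**6. Reading the table.** The discordant pattern is most common at small to moderate common change and rare when the change is large. Large common change is not safer, though: the support arm read alone is then significant in nearly every null trial (99% at 0.5 SD).

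**The case against.** The strongest reply is that the article never assigns the paired tests to the secondary outcomes. The sentence could describe follow-up contrasts after the interaction test, or supplementary tests on every variable, and a condensed article may leave the secondary model to a fuller document. The first part stands: the link is an inference from the restriction of the interaction test to the primary variables and from the wording of the quality-of-life aim. The second part carries less weight, because the article is not silent on change. It names a method, and that method does not estimate the randomised contrast.

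Other objections also stand in part:

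- Within-group tests do answer the quality-of-life aim as literally worded. They do not support attributing the change to the intervention.
- The Discussion sentence on wellbeing is conditional and reports no conclusion. The same section stresses comparison with controls, so the intent appears to be between-arm.
- The Background says only that NIV can bring improvement, and that patients often reject or misuse it. Common improvement is plausible, not assured. Regression to the mean on EQ-5D or HADS is not shown either, since no one is selected on those scores.
- The 16% to 25% figures hold only for common changes of about 0.2 to 0.33 SD at 75 per arm, under a decision rule the article does not state.

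A reader might infer that every secondary outcome is fixed to within-arm tests alone, or that false claims are expected at about 25%. The documents support neither. Survival is a secondary outcome that no paired test could analyse, and the rate depends on an unknown common change.

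**Conclusion.** The concern holds in a limited form. For EQ-5D and the psychological and clinical scales, the article states no test of the randomised contrast, and the only test of change it names outside the primary variables is within-group. None of the objections supplies the missing comparison.

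The size is illustrative. It rests on 1:1 allocation with 75 per arm, an equal true change in both arms and an assumed reading of the two p values. Under these, the misleading pattern ranges from 1% to 25% per outcome and time point, against about 5% for a between-arm test on change.

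The point should be fixed but does not threaten the trial: the primary outcome is already tested between arms. Survival lies outside this point.

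**What to change.** In Proposed analyses, state that for each continuous secondary outcome the inferential analysis is the between-arm difference at T1, T2 and T3, from a mixed model or ANCOVA adjusted for that outcome's T0 value, reported with a 95% confidence interval. State which outcomes the before-after results cover, and label them descriptive.

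The cost is a few sentences. T0 values are already collected, the sample size does not change, and the follow-up schedule is untouched. Recruitment is described as ongoing, so the change can be made before the final analysis, through the amendment route the article already describes (ethics committee and trial register).

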### Randomisation

#### Sequence generation

The patients will be randomised through a simple method, extracting a unit from the population using a method which guarantees the causality of the extractions (https://www.random.org).

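### The aim of finding who benefits from psychological support is paired with a baseline regression that, as worded, shows prognosis only; no treatment-by-baseline interaction is named

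*Protocol article*

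**What the plan says.** The Objectives section names two separate prediction aims among the secondary aims. One is "identification of psychological and clinical factors that predict rejection or misuse of NIV". The other is to identify "factors that predict the success of the psychological intervention".

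The Proposed analyses section gives one method that can serve either: "Multiple regression will be used to assess the influence of baseline variables on outcome indicators and identify predictor variables". The same section plans a treatment-by-time interaction for the primary outcomes, acceptance and adherence. It names no interaction between treatment and a baseline variable. A single 5% significance level is set and no adjustment for multiple tests is stated. The article does not list which baseline variables will be entered.

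On size, the Sample size section says "we anticipate that the study will require 150 subjects", within a range of 128 to 172.

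**The concern.** The two aims ask different things. Who rejects or misuses NIV is a question of prognosis, and relating baseline variables to outcome answers it. Who succeeds because of the intervention is a question of difference between arms: does the effect of support depend on the baseline factor? A regression of outcome on baseline variables does not estimate that difference. Fitting it in the experimental arm alone does not help, because a factor that predicts outcome in both arms also predicts it among the treated.

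The risk is that a general marker of good adherence is reported as a marker of response to psychological support. The question matters in this trial. The Design and interventions section makes the number of sessions depend on patient need and uses cognitive scores to help decide on extra components, and the Discussion presents tailoring as a strength. A finding about who benefits would therefore be of practical interest to readers.

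**Working it through.** **The plan's own figures.** The article gives no calculation for the regression, only for the overall comparison: "We will recruit between 128 subjects (statistical power of 0.80") up to 172 at power 0.90. No effect size is printed. With a two-sided 5% two-sample t test, equal arms and an assumed d = 0.50, the requirement is 63.77 per arm (128 in total) for 80% power and 85.03 per arm (172 in total) for 90%. The stated totals are reproduced, and power at 150 is 0.86. They are not in dispute.

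**Inputs.** N = 150 and alpha = 0.05 come from the article. Equal allocation (75 per arm) is assumed, since no ratio is stated.

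**Can the stated regression tell prognosis from benefit?** Take a standardised baseline factor and residual SD 1. With equal arms, the pooled coefficient is the average of the two arm-specific slopes.

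- Pure effect modifier, slope 0.5 in the treated arm and 0 in controls: 0.5 × 0.5 + 0.5 × 0 = 0.25.
- Pure prognostic factor, slope 0.25 in both arms: 0.5 × 0.25 + 0.5 × 0.25 = 0.25.

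The coefficients are identical. In simulation (4000 runs each, N = 150, treatment included as a covariate), the factor was significant in 82% of runs for the modifier and 86% for the prognostic factor. When the treatment-by-factor product was added, its test was significant in 85% of runs for the modifier and 5% for the prognostic factor. The interaction term makes the distinction; the model without it does not.

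**How large an interaction can be seen?** An evenly split binary moderator gives four cells of N/4 patients. In SD units the standard error of the interaction is √(4 ÷ (N/4)) = 4/√N.

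- N = 150: 4/12.25 = 0.327. Detectable at 80% power: (1.96 + 0.84) × 0.327 ≈ 0.92 SD, twice the 0.46 SD detectable for the overall effect with 75 per arm.
- Power for an interaction of 0.5 SD: Φ(0.5/0.327 − 1.96) = 0.33. For 1.0 SD: Φ(1.0/0.327 − 1.96) = 0.86.

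**False predictors if many candidates are entered.** The number of candidates k is an assumption. From the Assessment section:

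- Clinical 8, psychological 11 and cognitive 6 scores: 8 + 11 + 6 = 25.
- Adding 17 sociodemographic items and one work-productivity instrument: 25 + 17 + 1 = 43.
- An intermediate count using instrument totals is 34.

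Under a global null, expected false positives per outcome are k × 0.05. The chance of at least one is 1 − 0.95^k for independent tests; a simulated joint regression (4000 runs, predictor correlation 0 or 0.3) gives lower values.

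| k | Expected false positives | Chance of at least one: simulated to formula |
|---|---|---|
| 25 | 1.25 | 0.67 to 0.72 |
| 34 | 1.70 | 0.77 to 0.83 |
| 43 | 2.15 | 0.84 to 0.89 |

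**The case against.** The strongest reply is that multiple regression can carry interaction terms, that the article does not exclude them, and that model terms and predictor lists belong in a statistical analysis plan that is not shown. Part of this stands. The absence of a predictor list or selection rule is not a fault of a journal article, and the text does not say that only main effects will be fitted. But the article does not leave the matter open. It names a method and says what the method assesses, the influence of baseline variables on outcomes, and that is not what the second aim asks. It also specifies an interaction elsewhere in the same section, for time only.

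Three stronger readings are tempting and are not supported.

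- A reader might infer that the whole baseline battery, some 43 variables, will be entered and that spurious predictors are therefore certain. The article says only that baseline variables will be used. For rejection or misuse the aim refers to psychological and clinical factors, which leaves out most of the sociodemographic list. The counts above are illustrations, and the result is a probability under a null.
- A reader might infer that rejection of NIV is a yes/no event and that linear regression is therefore wrong. The article nowhere defines rejection as binary. Its stated measures are hours of use and prescribed minus effective hours, for which regression is suitable.
- A reader might infer that patients will be selected for support on these results. No such rule is proposed, and the aim is secondary.

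**Conclusion.** The point holds as a mismatch between one secondary aim and the analysis stated for it. As worded, the regression identifies prognostic factors; it does not identify factors that predict the success of the intervention. The size is best shown by the equal pooled coefficients (0.25 and 0.25) for a pure modifier and a pure prognostic factor, under equal arms and residual SD 1.

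Even with the right model, the trial can detect only large interactions: about 0.92 SD for an evenly split binary factor at N = 150. An exploratory label is therefore needed. The false-positive figures (1.25 to 2.15 per outcome, with a 0.67 to 0.89 chance of at least one) hold only if 25 to 43 candidates are all entered without adjustment. They support a short list and are not a forecast of what the trial will report.

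The regression on baseline variables is appropriate for the aim on rejection or misuse. The primary comparison and the sample size are not affected.

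**What to change.** In Proposed analyses, separate the two prediction aims.

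- **Success of the intervention:** fit models on both arms with treatment, the baseline factor and their interaction, for a short list of factors fixed before the data are analysed. Base any claim on the interaction estimate and its confidence interval, and label the analysis exploratory.
- **Rejection or misuse of NIV:** keep the regression on baseline variables, also with a short prespecified list. Use logistic regression only if rejection is analysed as yes/no.

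Which factors go on the lists is for the investigators to decide. The data are already planned for collection and the article reports that recruitment is ongoing, so the change is to analysis wording and can be made before results are known. The downside is that fewer predictors can be claimed.

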## Discussion

We anticipate some limitations or threats to the efficacy of the study protocol. First, the rigorous RCT design will be in contrast with the ‘single-patient’ approach. As part of the ‘single-patient’ approach patients will be free to choose the setting in which they receive the intervention; this may make it difficult to achieve an even distribution of settings. Third, patients who choose to use telemedicine might face difficulty accessing the intervention owing to technical problems.

Despite these limitations the design has many strengths. It investigates a form of psychological support specifically designed to facilitate adaptation to NIV. Moreover, the intervention will be tailored to patients’ needs and clinical status. The study protocol is projected in order to reduce barriers to participation such as disabilities (i.e. movements, dyspnoea) and practical barriers (daily activities and habits). Finally, to reduce the Hawthorne effect the experimental condition will be compared with an active control group, which will watch films related to the management of many aspects of COPD.

This study has the potential to demonstrate the viability of an easy-access intervention based on a ‘single-patient’ approach that can be used in several settings to facilitate adaptation to NIV and improve the QoL of COPD patients. This study protocol describes the development of the study design and the related intervention. If the hypothesis is confirmed, the intervention will have positive effects on physical and psychological wellbeing, and consequently reduce the costs of health care for COPD patients.

